##### Logical Memory

This task is from the Wechsler Memory Scale (WMS-III) [58]. It is a measure of semantic memory. Participants are presented with two brief stories and must recall information from these stories immediately and after a delay of between 10 and 20 minutes. Logical Memory has good test-retest reliability, is not susceptible to practice effects, and norms are available [57]. Logical Memory has been shown to be sensitive to the effects of aging and neuropsychological impairment [57]. Scores include the number of themes recalled and the amount of specific content information recalled [57].

##### Digit Span

This is a task from the Wechsler Memory Scale (WMS-III) [58]. It is a measure of working memory. Participants are presented with a number sequence and must immediately recall the numbers. The task progresses in difficulty as number sequences increase in length (minimum = 2 digits, maximum = 9 digits). Digit Span has two components. In the first part participants must recall the number sequences in the order presented (Digits Forward). In the second part participants must recall the number sequences in the reverse order to which they were presented (Digits Backward). Digit Span has good test-retest reliability, is not susceptible to practice effects and norms are available. Scores include the number of correctly recalled digits forward, the number of correctly recalled digits backward, and the total number of correctly recalled digits.

##### California Older Adult Stroop Test (COAST)

Stroop Tests are a common measure of executive functioning. COAST has been specially developed for use with geriatric populations [59]. It has three components. For the first task participants must identify the names of colours. For the second task participants must read colour name words. In the final task participants must identify the colour in which each colour name word is printed (e.g. the word RED is printed in green ink, so the correct participant response is "Green"). Stroop Tests generally have shown good test-retest reliability and only modest practice effects [57]. Stroop Tests have also been shown to be sensitive to the effects of aging and neuropsychological impairment, and some norms are available [57]. Scores include completion time, number of errors and number of self-corrected errors.

##### Sorting Test

This task is from the Delis-Kaplan Executive Function Scale (DKEF-S) [60]. Participants are presented with a set of six cards. The cards have words printed on them, and vary in colour and size. There are up to eight ways (rules), according to which the cards may be sorted into groups of three. In the Free Sorting condition, participants must sort the cards in as many different ways as possible and identify the rule by which they have sorted. The Sorting Test has been shown to be sensitive to the effects of aging and neuropsychological impairment [57]. The Sorting Test has good test-retest reliability and norms are available [60]. Scores include the number of correct sorts and the number of correct rule descriptions.

##### Matrix Reasoning

This is a task from the Wechsler Adult Intelligence Scale (WAIS) [61]. It is a measure of executive functioning. Participants are presented with a visual pattern that has one part missing. Participants must select, from multiple choice options, the picture which completes the pattern. The patterns progress in difficulty. Matrix Reasoning has good test-retest reliability and norms are available [61]. The score is the number of patterns correctly solved.

##### Symbol Digit Modalities Test (SDMT)

This is a measure of psychomotor speed [62]. It is a written task requiring participants to substitute numbers for symbols according to a key. Participants must complete as many substitutions as possible in 90 seconds. The SDMT has good test-retest reliability, is not susceptible to practice effects and is sensitive to the effects of aging and neuropsychological impairment. Norms are available [57]. The score is the number of correct substitutions.

##### Timed Instrumental Activities of Daily Living (TIADL)

This is a measure of applied information processing speed [63]. Participants complete five common tasks of daily living, according to set instructions. These tasks cover communication, money, food preparation, shopping, and medications, and incorporate actual everyday objects [63]. The score is based on the time taken to complete each task, with an adjustment for any errors.

##### Simple reaction time

Simple Reaction Time tasks are frequently used to measure psychomotor speed [64]. Computer-based, these tests require participants to press a button when a stimulus (e.g. a light or object) appears on the screen. Marked slowing of reaction time is evident with age and neurological impairment. Consistent with current practice [64], a Simple Reaction Time Task was developed specifically for this project. The Simple Reaction Time Task is run on a Toshiba Tecra A2 Laptop. For this task, 4 taps (faucets) are presented horizontally (and equidistant) across the screen. Participants are required to press the Space Bar when water starts to drip from one of the taps. A warning tone and message ("Get Ready") appear at the top of the screen before each trial. To avoid anticipatory responses, the interval between the warning and stimulus onset is variable. Participants complete 50 trials, with response time recorded in milliseconds from stimulus onset. Responses less than 100 millseconds are considered invalid. Scores are mean reaction time and standard deviation of reaction time.

##### Choice reaction time

Choice Reaction Time Tasks assess speed and concentration [64]. In these tests participants are presented with one stimulus and multiple response options. Responses are usually more delayed than in Simple Reaction Time Tasks, because participants must make a decision before responding [64]. The Choice Reaction Time Task was also developed specifically for this project. The Choice Reaction Time Task is run on a Toshiba Tecra A2 Laptop. For this task, 4 taps (faucets) are presented horizontally (and equidistant) across the screen. The keys D, F, J and K correspond to each tap in order from left to right. Participants are instructed that when water starts to drip from one of the taps, they are to press the corresponding key. A warning tone and a message ("Get Ready") at the top of the screen precede each trial. To avoid anticipatory responses, the interval between the warning and stimulus onset is variable. Participants complete 50 trials, with response time recorded in milliseconds from stimulus onset. Any errors are also recorded. Responses less than 100 millseconds are considered invalid. Scores are mean reaction time, standard deviation of reaction time, and number of errors.

#### Primary outcome measures: aerobic capacity and strength

##### Six-Minute Walk Test (SMWT)

This is adapted from the Senior Fitness Test [65]. It is a functional measure of aerobic endurance. A rectangular course, measuring 3 m × 15 m, is marked out for participants to walk around. Two chairs are placed inside the course for participants who need to rest during the test. The score is the number of metres walked in six minutes. The number of rests taken or adaptations used (e.g. walking sticks etc) is noted with the score.

##### Modified Astrand-Ryhming Cycle Ergometer Test

This is a multi-stage, sub-maximal exercise test, modified from the Astrand-Ryhming protocol [51]. It is conducted on a cycle-ergometer and is a measure of aerobic fitness. This test is similar to the Astrand-Ryhming protocol, except that work-rate is adjusted after the second minute, according to heart-rate and age (see Table 3). The initial power level is set at 0.5 kp for sedentary older women, and 1.0 kp for sedentary older men. This modified protocol is regularly used with clinical populations in research conducted at the School of Human Movement Studies, University of Queensland. The Astrand-Ryhming nomogram (including the age correction factor) is used to estimate maximal oxygen uptake (VO_2_max) [51].

**Table 3 T3:** Power alterations according to age and heart rate after 2^nd ^minute (beats per minute)

	Heart rate 65 years old	Heart rate 70 years old	Heart rate 75 years old
Raise power level by			
1.0 – 1.5 kp	<92.5	<90	<87.5
0.5 – 1.0 kp	92.5 – 111.5	90 – 109	87.5 – 106.5
≤ 0.5	112.5 – 121.5	110 – 119	107.5 – 116.5
Lower power level by			
0.5 – 1.0 kp	>142.5	>140	>137.5
≤ 0.5 kp	132.5 – 141.5	130 – 139	127.5 – 136.5

##### 30-Second Chair Stand

This is taken directly from the Senior Fitness Test [65]. It is a functional measure of lower body strength. Participants are seated in a chair, with feet flat on the floor. The score is the number of full stands completed in 30 seconds, with arms folded across the chest. Any use of adaptations (e.g. pushing off the legs, using the arms of the chair) is noted with the score.

##### Arm Curl

This is taken directly from the Senior Fitness Test [65]. It is a functional measure of upper body strength. Participants are seated in a chair and given a small dumbbell (2 kg for women, 4 kg for men). The score is the number of bicep curls completed in 30 seconds. Any adaptations (e.g. use of a lighter weight) are noted with the score.

#### Secondary outcome measures: Anthropometrics and physiology

##### Anthropometrics

Measures of height (cm), weight (kg), hip girth (cm) and waist girth (cm) are taken using standard protocols [51].

##### Resting heart rate

Resting heart rate is measured by palpation of the radial artery while participants are seated. The number of beats recorded in 10 seconds is multiplied by 6, to give beats per minute.

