### Sample size

Ninety-nine participants will be recruited for the study. A sample size of 12 participants in each of the three groups would enable detection of a within-group difference, from baseline to post-test, of 1 item (SD = 1.1) on Digit Span and 184 milliseconds (SD = 198) on Choice Reaction Time. Twenty participants in each group would enable detection of a between-group difference, at post-test, of 2 items (SD = 2.2) on Digit Span. Twenty-nine participants in each group would enable detection of a between-group difference, at post-test, of 118.8 milliseconds (SD = 160) on Choice Reaction Time. These sample size calculations assume a two-tailed alpha level of 0.05 and a power of 80%. The effect sizes and standard deviations are based on results from previous studies of physical activity for cognitive functioning in older adults (e.g. [11,49]). To account for attrition over time, the required sample size (29) is increased by 10% to 33 participants per group.

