### Intervention

#### Exercise-only training

Participants in this group receive three gym-based sessions per week for 16 weeks. Each session lasts for 60 minutes and includes progressive aerobic and strength training. Each session includes a maximum of 10 participants and is supervised by at least one qualified fitness instructor.

The progression of the aerobic training is adapted from the ACSM Guidelines for Exercise Testing and Prescription [51]. Intensity is prescribed using percentage of Heart Rate Reserve (HRR). Participants on medications which attenuate heart rate (e.g. beta-blockers) are prescribed exercise intensity using Rate of Perceived Exertion (RPE; [52]). The relative progressions of intensity and duration can be seen in Table 1. Intensity is monitored with Polar A3 heat rate monitors. Participants complete the aerobic training on treadmills, stationary bicycles, cross-trainers, and stationary rowing machines.

**Table 1 T1:** Duration and intensity progression of aerobic training

**Week**	**Duration (min)**	**Intensity (% HRR)**	**Intensity (RPE)**
1	20	50 – 60	9 – 11
2	20	50 – 60	9 – 11
3 – 5	25	60 – 70	11
6 – 8	30	60 – 70	11
9 – 11	30	70 – 80	11 – 13
12 – 14	35	70 – 80	11 – 13
15 & 16	40	75 – 85	13 – 15

Strength is assessed, and intensity prescribed, for each participant in the first gym session. Progress is monitored and prescribed by the fitness instructor. The strength training includes exercises to target major muscle groups in the upper body, lower body, and core. The upper and lower body exercises use free weights and machines. The core exercises use a swiss-ball.

Participants stretch major muscle groups at the end of each session.

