### Measurements

The primary outcome measures are indicators of cognitive functioning, aerobic capacity and strength. Secondary outcome measures are anthropometric measurements, resting heart-rate, blood pressure, indicators of psychological well-being and participant perceptions. All measures are assessed at baseline, post-test, and 6-month follow-up, except for the qualitative feedback which is assessed only at post-test.

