### Analyses

Analysis of variance techniques will be used to assess changes over time (baseline, post-test, follow-up), and differences between groups, on the measures of aerobic capacity and cognitive functioning. Mean scores and variability scores will be used in these analyses. Variability scores may provide a more sensitive indicator than mean scores, of changes in cognitive functioning in older adults [71]. Where appropriate age, education and gender will be included as covariates. The Reliable Change Index will be used to determine the percentage of participants who demonstrate a significant change in performance, relative to their individual baseline [72,73]. This approach may provide a more accurate picture of changes experienced by participants than simple group differences [72,73]. Regression techniques will be used to identify the influence of changes in aerobic capacity on cognitive functioning. Regressions techniques will also be used to identify the influence of changes in psychological wellbeing on cognitive functioning.

The qualitative data will be analysed to identify themes related to participant perceptions of the program.

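### Resting heart rate is scored as a 10-second count times six, so readings move in 6 bpm steps and lose precision that a 60-second count would largely recover

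*Protocol article*

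**What the plan says.** The Resting heart rate section of the protocol article fixes the method in two sentences. The first reads "Resting heart rate is measured by palpation of the radial artery while participants are seated". The second gives the scoring rule: "The number of beats recorded in 10 seconds is multiplied by 6, to give beats per minute". The section states no repeat reading, averaging or longer count.

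The Measurements section gives the outcome its status: "Secondary outcome measures are anthropometric measurements, resting heart-rate, blood pressure, indicators of psychological well-being and participant perceptions". It also sets the timing: "All measures are assessed at baseline, post-test, and 6-month follow-up, except for the qualitative feedback which is assessed only at post-test".

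The Analyses section applies analysis of variance to change over time and to "differences between groups, on the measures of aerobic capacity and cognitive functioning". It does not name resting heart rate.

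The Sample size section requires 29 per group and raises this to 33 for 10% attrition. That calculation is for Choice Reaction Time. No calculation in the section concerns heart rate.

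**The concern.** A whole-beat count multiplied by six can give only values such as 60, 66, 72 and 78 bpm. One beat more or less at the edge of the window moves the score by 6 bpm, and any recorded change is zero or a multiple of 6. That is coarse for an outcome followed over time in about 29 people per arm. If change from baseline is analysed, the counting error enters twice and is set against the spread of within-person change. At stake is the precision of one secondary outcome: real differences become harder to see and confidence intervals wider than they need be.

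**Working it through.** **Inputs from the protocol article.** Window 10 seconds and multiplier 6 (Resting heart rate); three visits (Measurements); 29 per group before attrition, two-sided alpha 0.05, power 80% (Sample size).

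**Assumed, because the documents give no heart-rate SD.** Between-person SD 9 bpm. SD of true within-person change 6 bpm, with 5, 8 and 10 bpm as alternatives.

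**1. The plan's own figures.** The multiplier is right: 60/10 = 6. The group size also reproduces: 2 × (1.96 + 0.84)² × (160/118.8)² = 28.5, so 29; and 29/0.9 = 32.2, so 33. I use 29 below because 33 is the recruitment target.

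**2. Counting error per reading.** For a window of T seconds the step is 60/T bpm. The error SD is step/√12 if timing starts on a beat and step/√6 if it starts at a random point between beats.

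| Window | Step (bpm) | SD, one reading (bpm) | SD, change score (× √2) |
|---|---|---|---|
| 10 s | 6 | 1.73 to 2.45 | 2.45 to 3.46 |
| 30 s | 2 | 0.58 to 0.82 | 0.82 to 1.15 |
| 60 s | 1 | 0.29 to 0.41 | 0.41 to 0.58 |

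Error variance goes with the square of the step. A 60-second count therefore leaves 1/36 = 2.8% of it and removes about 97%.

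**3. Arms compared at post-test only.** The error enters once, with variance 36/12 = 3 to 36/6 = 6. Against 9² = 81, added variance is 3/81 = 3.7% to 6/81 = 7.4%. Effective sample is 29/1.037 = 28 to 29/1.074 = 27 per arm.

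**4. Change from baseline.** The error enters twice, with variance 6 to 12. Effective n = 29/(1 + added variance).

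| SD of true change (assumed) | Added variance | Effective n per arm | Loss of effective sample |
|---|---|---|---|
| 5 bpm | 6/25 = 24% to 12/25 = 48% | 23.4 to 19.6 | 19% to 32% |
| 6 bpm | 6/36 = 17% to 12/36 = 33% | 24.9 to 21.8 | 14% to 25% |
| 8 bpm | 6/64 = 9% to 12/64 = 19% | 26.5 to 24.4 | 9% to 16% |
| 10 bpm | 6/100 = 6% to 12/100 = 12% | 27.4 to 25.9 | 6% to 11% |

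**5. The same loss as power, at a change SD of 6 bpm.** Take an effect with 80% power when there is no counting error and 29 per group. Power is 68% to 74% with the 10-second count and about 80% with a 60-second count. The detectable difference, 2.80 × √(36 + error variance) × √(2/29), is 4.77 to 5.10 bpm with 10 seconds and 4.42 to 4.43 bpm with 60 seconds.

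**6. Bias.** In a simulation of 400,000 people with a true mean change of −3 bpm and a change SD of 6 bpm, the 10-second rule returned −2.99 under either way of starting the clock. The SD of recorded change rose from 6 to 6.48 or 6.93, which matches √42 and √48.

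**The case against.** The strongest reply is that this is a choice of measurement technique on a peripheral outcome. No aim, hypothesis or sample-size calculation names resting heart rate, and the protocol neither contradicts itself nor misstates anything here. That stands, and it keeps the point minor.

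It is also fair to say that the larger figures need a change-score analysis. Measurement at three visits makes one plausible, but the Analyses section does not state it for this outcome, and the between-group sample-size calculations are for differences at post-test. On a post-test comparison the cost is only about 4% to 7% of variance under the assumed SD. Both cases therefore have to be shown.

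Three stronger readings are tempting and are not supported:

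- **That the rule biases the group contrast.** If timing starts on a beat and only completed intervals are counted, readings are low by half a step on average. One convention used throughout shifts all arms and visits alike, so this cancels. The Blinding section says researchers are unblinded, but nothing in the document shows that counts would be shaded by arm.
- **That the trial has heart-rate monitors to hand for this measurement.** The article says "Intensity is monitored with Polar A3 heat rate monitors", but only for training sessions, which take place at a private gym. Physical assessments are at the University. Who owns the monitors, and whether they are available at assessments, is not stated.
- **That a longer count abolishes the error.** It reduces it to a 1 bpm step and leaves biological variation untouched.

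**Conclusion.** The point holds as a minor, cheap improvement. The 6 bpm step follows directly from the stated rule. The counting-error SD of 1.73 to 2.45 bpm per reading needs only the two ways of starting the clock. Nothing elsewhere in the article offsets it.

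How much this costs depends on two things that the documents do not give: the SD of heart rate or of its change, and the analysis used for this outcome. Added variance is about 4% to 7% for a post-test comparison at an assumed SD of 9 bpm, and 17% to 33% for change from baseline at an assumed SD of 6 bpm. Across change SDs of 5 to 8 bpm, the loss of effective sample is 9% to 32%. The harm is to precision only. The primary outcomes and the sample size are unaffected.

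**What to change.** In the Resting heart rate section, replace the 10-second count with a seated 60-second count, recorded as counted. Use it in all arms and at all three visits.

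Keep the 10-second count for any participant whose baseline is already taken. Switching within a person could create an artificial change: with timing from a beat, the average shortfall is half a step, which is 3 bpm at 10 seconds and 0.5 bpm at 60 seconds, a difference of 2.5 bpm.

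The cost is about 50 seconds in a 30-minute physical assessment. With 99 participants and three visits this is at most 99 × 3 × 50 = 14,850 seconds, or about 4 hours over the whole trial. It needs no new equipment or staff.

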##### Blood pressure

Diastolic and systolic blood pressure (mm Hg) are measured using standard protocols [51].

#### Secondary outcome measures: Psychological well-being

##### Memory Complaint Questionnaire (MAC-Q)

This is a six-item scale of self-reported memory decline [66]. Participants rate current memory ability against past performance for given situation (e.g. remembering the name of a person just introduced to you), on a 5-point scale from *much better now *to *much worse now*. The scale reliability is .57, with test-retest reliability of .67 [66]. Scores are summed, with double weighting for the final item (a comparison of general memory abilities). A higher score indicates greater self-reported decline.

##### SF-36: Mental Health

The Mental Health component score from the Medical Outcomes Study Short Form (SF-36; [67] reflects emotional wellbeing as measured on four subscales: vitality (items on energy and fatigue), social functioning (items on the impact of physical and emotional health on social activities), role-emotional (items on the impact of emotional problems on everyday activities), and mental health (items on happiness, nervousness and depression). The SF-36 is a widely used measure of wellbeing and Australian norms are available. A scoring algorithm is provided in the manual [68].

##### Goldberg Anxiety and Depression Scale (GADS)

This is an 18-item measure of symptoms of anxiety and depression, derived from psychiatric interview protocols [69]. Participants answer *Yes *or *No *to questions about their feelings in the past month, such as *have you been irritable? *and *have you felt hopeless? *The scale has been validated against clinical diagnoses of anxiety and depression, and found to have good specificity and sensitivity [69]. Higher scores reflect increased symptoms of anxiety and depression.

##### Health-Related Hardiness Scale (HRHS)

This scale assesses health-related hardiness, a "personality construct that moderates the stress-illness relationship" [70]. The construct is comprised of three dimensions: control, commitment, and challenge. The control dimension is associated with a sense of control over one's health and confidence in one's skills for managing health. The Control subscale of the HRHS is used in this study. Participants respond to items such as *I can avoid illness if I take care of my self*, on a 6-point scale from *strongly disagree *to *strongly agree*. The Control sub-scale reliability is .91, with test-retest reliability of .76 [70]. Higher scores reflect an increased sense of control over health.

